### Exploratory endpoints:

- total control rate (TCR: no vomiting, rescue medications, or nausea) and complete control rate (CCR: no vomiting/rescue medications, only grade 1 or less nausea) during acute, delayed, long-delayed, and overall post-chemotherapy phases.
- CINV incidence patterns and daily occurrence rates across each period.

|                                  |                                                                                                                                                                                                                                                                                                                                                                                                                                                                                                                                                                                                                                                                                                                                                                                                                                                                                                                                                                                                                                                                                                                                                                                                                                                                                                                                                                                                   |
|----------------------------------|---------------------------------------------------------------------------------------------------------------------------------------------------------------------------------------------------------------------------------------------------------------------------------------------------------------------------------------------------------------------------------------------------------------------------------------------------------------------------------------------------------------------------------------------------------------------------------------------------------------------------------------------------------------------------------------------------------------------------------------------------------------------------------------------------------------------------------------------------------------------------------------------------------------------------------------------------------------------------------------------------------------------------------------------------------------------------------------------------------------------------------------------------------------------------------------------------------------------------------------------------------------------------------------------------------------------------------------------------------------------------------------------------|
| 
Inclusion Criteria
 | 
Patients must meet all of the following criteria to be eligible for the study:
 
 
1. Age 18-75 years.
 
2. Diagnosed with malignant tumors and receiving chemotherapy with moderate to high emetic risk.
 
3. ECOG performance status 0-1.
 
4. Expected survival <math>\geq 12</math> weeks at screening and able to receive at least one cycle of the current chemotherapy regimen.
 
5. Adequate organ function meeting the following criteria:           
 
a: Neutrophil count <math>\geq 1.5 \times 10^9/L</math>;
 
b: Platelet count <math>\geq 100 \times 10^9/L</math>;
 
c: In patients without known liver metastases, aspartate aminotransferase <math>\leq 3 \times ULN</math> and/or alanine aminotransferase <math>\leq 3 \times ULN</math> (for patients with liver metastases, it can be relaxed to <math>\leq 5 \times ULN</math>);
 
 
 
6. Fertile subjects agree to use reliable contraception (e.g., condoms, contraceptive foam, IUD) throughout the study. Postmenopausal women (<math>>1</math> year) and subjects with bilateral oophorectomy, bilateral vasectomy, or bilateral tubal ligation are exempt.
 
7. Voluntarily participating in the study with signed informed consent and good compliance.
 
 |
| 
Exclusion Criteria
 | 
Patients with any of the following conditions are not eligible for the study:
                                                                                                                                                                                                                                                                                                                                                                                                                                                                                                                                                                                                                                                                                                                                                                                                                                                                                                                                                                                                                                                                                                                                                                                                                                                                                                              |

1. Received radiotherapy within 1 week before chemotherapy.
2. Other diseases causing nausea or vomiting, such as gastrointestinal obstruction or central nervous system malignancies.
3. Vomiting, nausea, or mild nausea symptoms within 24 hours before treatment.
4. Concurrent use of corticosteroids or any other antiemetic drugs.
5. Contraindications to corticosteroids.
6. Cognitive impairment (e.g., dementia or severe learning difficulties) that prevents completion of nausea/vomiting assessment scales.
7. Use of antipsychotic drugs within 30 days before or during treatment.
8. Severe uncontrolled diseases affecting the liver, kidneys, cardiovascular system, respiratory system, endocrine system, or central nervous system.
9. Allergy to study drugs.
10. Pregnant or breastfeeding women.
11. Participation in another clinical study involving investigational drugs or devices within 3 months before screening.

|                            |                                                                                                                                                                                                                                                                                                                                                                                                                                                                                                                                                                                                                                                                                                        |
|----------------------------|--------------------------------------------------------------------------------------------------------------------------------------------------------------------------------------------------------------------------------------------------------------------------------------------------------------------------------------------------------------------------------------------------------------------------------------------------------------------------------------------------------------------------------------------------------------------------------------------------------------------------------------------------------------------------------------------------------|
|                            | 
12. Any other condition that the investigator deems a significant risk to the subject's health or safety or that may affect efficacy assessment.
                                                                                                                                                                                                                                                                                                                                                                                                                                                                                                                                                |
| Withdrawal Criteria | 
Patients will be withdrawn from the study if any of the following occurs:
 
 
1. Withdrawal of informed consent or request to exit the study and refusal of further follow-up.
 
2. Investigator deems it necessary to withdraw the patient (e.g., loss of freedom to express willingness due to imprisonment or quarantine).
 
3. Loss to follow-up.
 
4. Serious adverse events (SAEs) where risks outweighed benefits
 
5. Termination of the study by the sponsor, investigator, or regulatory authority.
 
                                                                                                         |
| Study Design        | 
This study is a randomized, non-inferiority trial with control and experimental groups, divided into screening and treatment phases.
 
 
1. Screening Phase           
 
• Assess eligibility criteria. Eligible patients proceed to the treatment phase.
 
 
 
2. Treatment Phase           
 
• Control Group: Intravenous injection of 8 mg dexamethasone 0.5 hours before chemotherapy and oral administration of single dose of NEPA (each containing 0.3 g netupitant and 0.5 mg palonosetron hydrochloride) 1 hour before chemotherapy.
 
 
 
 |

|                        |                                                                                                                                                                                                                                                                                                                                                                                                                                                                                                                                                                                                                                                                                                                             |
|------------------------|-----------------------------------------------------------------------------------------------------------------------------------------------------------------------------------------------------------------------------------------------------------------------------------------------------------------------------------------------------------------------------------------------------------------------------------------------------------------------------------------------------------------------------------------------------------------------------------------------------------------------------------------------------------------------------------------------------------------------------|
|                        | 
 
Experimental Group: Intravenous injection of 5 mg dexamethasone 0.5 hours before chemotherapy and oral administration of single dose of NEPA (each containing 0.3 g netupitant and 0.5 mg palonosetron hydrochloride) 1 hour before chemotherapy.
 
 
Stratification Factors: Gender, age, CINV risk factors, ECOG score, tumor type, distant metastasis of the tumor, emetic risk of the chemotherapy regimen, smoking history, alcohol consumption history, etc.
 
Discontinuation Criteria: Discontinue treatment if the patient experiences severe adverse events or specific types of adverse events, such as severe drug intolerance or allergic reactions.
 |
| Study Drugs     | 
 
Dexamethasone Sodium Phosphate Injection
 
Netupitant/Palonosetron Capsules (each containing 0.3 g netupitant and 0.5 mg palonosetron hydrochloride)
 
                                                                                                                                                                                                                                                                                                                                                                                                                                                                                                               |
| Dosing Schedule | 
Control Group: Intravenous injection of 5 mg dexamethasone 0.5 hours before chemotherapy and oral administration of 1 capsule of netupitant/palonosetron (each containing 0.3 g netupitant and 0.5 mg palonosetron hydrochloride) 1 hour before chemotherapy.
 
Experimental Group: Intravenous injection of 8 mg dexamethasone 0.5 hours before chemotherapy and oral administration of 1 capsule of netupitant/palonosetron (each containing 0.3 g netupitant and 0.5 mg palonosetron hydrochloride) 1 hour before chemotherapy.
                                                                                                                                                                              |

|                                          |                                                                                                                                                                                                                                                                                                                                                                                                                                                                                                                                                                                                                                                                                                                                                                                                                                                                    |
|------------------------------------------|--------------------------------------------------------------------------------------------------------------------------------------------------------------------------------------------------------------------------------------------------------------------------------------------------------------------------------------------------------------------------------------------------------------------------------------------------------------------------------------------------------------------------------------------------------------------------------------------------------------------------------------------------------------------------------------------------------------------------------------------------------------------------------------------------------------------------------------------------------------------|
|                                          | Discontinuation Criteria: Discontinue treatment if the patient experiences severe adverse events or specific types of adverse events, such as severe drug intolerance or allergic reactions.                                                                                                                                                                                                                                                                                                                                                                                                                                                                                                                                                                                                                                                                       |
| Data Collection                   | Data related to the study treatment will be recorded within 7 days after the patient completes chemotherapy. Past medical history data will be collected based on medical records and patient interviews and entered into an electronic data capture (EDC) system.                                                                                                                                                                                                                                                                                                                                                                                                                                                                                                                                                                                                 |
| Sample Size Calculation           | 186 subjects                                                                                                                                                                                                                                                                                                                                                                                                                                                                                                                                                                                                                                                                                                                                                                                                                                                       |
| Data Analysis/Statistical Methods | 
 
• Intention-To-Treat (ITT): Includes all randomized subjects, regardless of whether they completed the study, deviated from the protocol, or dropped out.
 
• Modified Intention-To-Treat (mITT): mITT is a variation of ITT that excludes certain participants post-randomization based on predefined criteria (e.g., major protocol violations, ineligibility, or lack of any post-baseline data).
 
• Per Protocol Set (PPS): includes only participants who fully adhered to the trial protocol (e.g., completed treatment, complied with visits, and had no major violations).
 
• All statistical analyses will be performed using SPSS 26.0 statistical software and RStudio v4.3.3. All statistical tests will be two-sided, with a significance level of <math>P \leq 0.05</math>.
 
 |

|                       |                                                                                                                                                                                                          |
|-----------------------|----------------------------------------------------------------------------------------------------------------------------------------------------------------------------------------------------------|
| Study Timeline | 

• First subject enrollment: October 2024

• Estimated last subject enrollment: August 2025

• Estimated study completion date: August 2025

 |
|-----------------------|----------------------------------------------------------------------------------------------------------------------------------------------------------------------------------------------------------|

## Study Flowchart

[figure not shown]

| Project                                                            | Screening Period | Baseline | Treatment Period |    |    |    |
|--------------------------------------------------------------------|------------------|----------|------------------|----|----|----|
| Visit Day                                                          | D-3~D0           | D0       | D1               | D3 | D5 | D7 |
| Informed Consent Signed                                            | x                |          |                  |    |    |    |
| Inclusion/Exclusion Criteria                                       | x                |          |                  |    |    |    |
| Randomization                                                      | x                |          |                  |    |    |    |
| Demographic Data                                                   | x                |          |                  |    |    |    |
| Medical History                                                    | x                |          |                  |    |    |    |
| ECOG Performance Status                                            | x                |          |                  |    |    |    |
| Physical Examination                                               | x                | x        | x                | x  | x  | x  |
| Vital Signs a                                           | x                | x        | x                | x  | x  | x  |
| Blood Glucose                                                      |                  | x        | x                | x  | x  | x  |
| Complete Blood Count b                                  | x                |          |                  |    | x  |    |
| Urinalysis c                                            | x                |          |                  |    |    |    |
| Biochemical Profile d                                   | x                | x        |                  |    | x  |    |
| Coagulation Function e                                  | x                |          |                  |    |    |    |
| Pregnancy Test f                                        | x                |          |                  |    |    |    |
| Thyroid Function Tests g                                | x                |          |                  |    |    |    |
| Viral Serology h                                        | x                |          |                  |    |    |    |
| Electrocardiogram (ECG)                                            | x                | x        | x                | x  |    |    |
| Echocardiography                                                   | x                |          |                  |    |    |    |
| Doppler Ultrasound (Liver, Gallbladder, Pancreas, Spleen, Kidneys) | x                |          |                  |    |    |    |
| PK Blood Sampling                                                  | x                |          |                  |    |    |    |
| Drug Dispensation                                                  |                  | x        | x                |    |    |    |
| Past/Concomitant Medications                                       | x                |          |                  |    |    |    |
| Adverse Events                                                     |                  | x        | x                | x  | x  | x  |
| Compliance with Study Medication i                      |                  | x        | x                |    |    |    |
| Rescue Therapy                                                     |                  | x        | x                | x  | x  | x  |
| Chemotherapy Assessment                                            |                  | x        | x                | x  | x  | x  |

**Notes:**

- \*Safety follow-up will be conducted within 7 days after the last administration of netupitant/palonosetron capsules.
- a. Vital Signs: Including body temperature, blood pressure, pulse, and respiratory rate. Blood pressure should be measured as systolic and diastolic pressures after resting in a seated position for 5 minutes, and measurements should be taken at the same time and with the same sphygmomanometer whenever possible.
- b. Complete Blood Count: White blood cell count (WBC), neutrophil count (NEUT), neutrophil percentage, lymphocyte count (LYMPH), lymphocyte percentage, monocyte count, monocyte percentage, eosinophil count, eosinophil percentage, basophil count, basophil percentage, red blood cell count (RBC), hematocrit (HCT), mean corpuscular volume (MCV), mean corpuscular hemoglobin (MCH), mean corpuscular hemoglobin concentration (MCHC), hemoglobin (Hb), platelets (PLT).

- c. Urinalysis: Protein (PRO), glucose (GLU-U), microscopic WBC, microscopic RBC, casts, occult blood.
- d. Biochemical Profile: Aspartate aminotransferase (AST), alanine aminotransferase (ALT), gamma-glutamyl transferase (GGT), lactate dehydrogenase (LDH), total bilirubin (TBIL), direct bilirubin (DBIL), total protein (TP), albumin (ALB), alkaline phosphatase (ALP), triglycerides (TG), total cholesterol (TC), sodium (Na+), potassium (K+), chloride (Cl), total calcium (Ca2+), glucose (GLU), urea (Urea) and/or blood urea nitrogen (BUN), creatinine (Cr), uric acid (UA).
- e. Coagulation Function: Prothrombin time (PT), activated partial thromboplastin time (APTT), thrombin time (TT), fibrinogen (FIB), international normalized ratio (INR), D-dimer (DD).
- f. Pregnancy Test: Only for women of childbearing potential. Blood pregnancy test will be conducted at the screening visit, and urine pregnancy test may be performed at other visits as deemed appropriate by the investigator.
- g. Thyroid Function: Free triiodothyronine (FT3), free thyroxine (FT4), thyroid-stimulating hormone (TSH).
- h. Viral Serology: Including hepatitis B surface antigen, hepatitis B surface antibody, hepatitis B e antigen, hepatitis B e antibody, hepatitis B core antibody, hepatitis C antibody, HIV antibody, syphilis antibody.
- i. Participants should ensure medication adherence as required by the protocol. If a dose is missed, the participant should continue taking the prescribed amount on the next day without doubling the dose.

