| Nature of the Study    | Investigator-Initiated Study                                                                                                                                                                                                                                                       |
| Study Design           | Prospective, Randomized, Non-inferiority Trial                                                                                                                                                                                                                                     |
| Study Population       | Patients with chemotherapy-induced nausea and vomiting (CINV) due to malignant tumors                                                                                                                                                                                              |
| Research Question      | To explore the clinical efficacy of different low-dose dexamethasone combined with single or double standard doses of netupitant/palonosetron capsules (NEPA) for the prevention of CINV.                                                                                          |
| Study Objectives       | Primary Objective:
To explore the efficacy of different low-dose dexamethasone combined with single dose of NEPA in preventing CINV.
Secondary Objectives:
To evaluate the safety of different low-dose dexamethasone combined with single dose of NEPA in treating CINV. |

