A 2023 open-label, randomized controlled study by Gao A et al. in patients receiving HEC regimens showed the superiority and good safety of double-dose fosaprepitant over single-dose fosaprepitant in preventing delayed-phase CINV when using the same doses of palonosetron and dexamethasone [18]. Inspired by this, we conducted a second round of trials based on the previous treatment study, selecting patients from the control and experimental groups who did not achieve complete absence of nausea and vomiting in the first cycle for a second cycle of treatment. The primary and secondary endpoints in the second cycle were self-controlled with those in the first cycle, exploring the efficacy and safety of single-day different low-dose dexamethasone combined with double-dose standard NEPA in preventing nausea and vomiting induced by moderately to highly emetogenic chemotherapy. Although NEPA has shown good safety in multiple clinical trials and clinical observations, there are limited studies on the use of multiple doses of netupitant and palonosetron capsules in preventing nausea and vomiting induced by MEC/HEC, and no studies have been conducted on the use of NEPA after chemotherapy. The instructions also state that NEPA should not be used to prevent nausea and vomiting after chemotherapy, making this an off-label use with unknown risks and the potential for unforeseen and severe toxicities and adverse effects.

Based on the existing safety clinical data of dexamethasone and netupitant and palonosetron capsules, adverse events reported by similar products, and the characteristics of the study population, the following measures have been taken in risk control: (1) Strictly adhering to the inclusion and exclusion criteria for participants, excluding those with severe, uncontrolled comorbidities, as well as diseases or clinical conditions that may interfere with the evaluation of the drugs; (2) Closely monitoring adverse events (AEs) in participants during the study, including AEs and AEs of special concern, such as significant gastrointestinal reactions and new drug-induced rashes, and providing suggested management measures; (3) Permitting rescue treatment in the trial at the investigator's discretion, including reducing the dose of dexamethasone, substituting other antiemetic drugs, delaying chemotherapy, reducing chemotherapy doses, or temporarily discontinuing chemotherapy.

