## **2. Research Objectives and Endpoint Goals**

### **2.1 Research Objectives**

#### **2.1.1 Primary Objective**

To explore the efficacy of single-day different low-dose dexamethasone combined with single dose of standard NEPA in preventing nausea and vomiting induced by moderately to highly emetogenic chemotherapy.

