## 5.2 Dosing Regimen

### 5.2.1 Drug Dose

- **Control Group:** 8 mg of dexamethasone is given intravenously 0.5 hours before chemotherapy, and 1 capsule of netupitant and palonosetron hydrochloride capsules (each capsule contains 0.3 g of netupitant and 0.5 mg of palonosetron hydrochloride) is taken orally 1 hour before chemotherapy.
- **Experimental Group:** 5 mg of dexamethasone is given intravenously 0.5 hours before chemotherapy, and 1 capsule of netupitant and palonosetron hydrochloride capsules (each capsule contains 0.3 g of netupitant and 0.5 mg of palonosetron hydrochloride) is taken orally 1 hour before chemotherapy.

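### The flowchart's missed-dose note does not fit a single pre-chemotherapy dose: unless chemotherapy is postponed, following it puts NEPA after chemotherapy has started

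*Protocol*

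**What the plan says.** **Regimen.** Protocol Sections 3.2 and 5.2.1 give both arms one dexamethasone injection 0.5 hours before chemotherapy and one NEPA capsule, which "is taken orally 1 hour before chemotherapy". Section 2.1.1 states the aim as "To explore the efficacy of single-day different low-dose dexamethasone combined with single dose of standard NEPA". Section 10.2 describes observation over one cycle.

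**Flowchart.** The rows "Drug Dispensation" and "Compliance with Study Medication" are ticked at D0 and again at D1. D0 is headed as baseline, and the columns under "Treatment Period" begin at D1. Footnote i is attached to the compliance row. It first asks for adherence as the protocol requires, then adds: "If a dose is missed, the participant should continue taking the prescribed amount on the next day without doubling the dose".

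**Label restriction.** Section 1.3.1 says: "The instructions also state that NEPA should not be used to prevent nausea and vomiting after chemotherapy". It adds that such use is off-label with unknown risks, and that no studies of NEPA given after chemotherapy have been done.

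**Synopsis.** The research question still refers to dexamethasone "combined with single or double standard doses of netupitant/palonosetron capsules (NEPA"), while the objectives just below it specify a single dose.

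**The concern.** A next-day rule for missed doses suits a drug taken daily. Here the capsule is prophylactic, is given once, and is tied to a time before the infusion. A site or patient who follows the footnote after a missed capsule would give NEPA once chemotherapy was under way, which is the use that the Protocol itself warns against. Staff work from the flowchart at the bedside, so a wrong instruction there can be acted on even when the dosing section is right. What is at stake is an avoidable off-label exposure in an occasional patient.

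**Working it through.** The Protocol states no figure to reproduce. The check sets the dosing text against the footnote.

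**1. Is there a later scheduled dose for the footnote to refer to?** No. Sections 3.2 and 5.2.1 schedule one capsule, the objectives say single dose, and Section 10.2 limits observation to one cycle.

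**2. When does the next day fall?** The flowchart does not state whether D0 or D1 is the dosing day, so both readings are tested.

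| Dosing day | Next day | Relation to chemotherapy, if given as planned |
|---|---|---|
| D0 | D1 | After it has started |
| D1 | D2 (no flowchart column) | After it has started |

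The answer is the same either way. As an illustration, assume the capsule is taken at the same clock time a day later. It was due at -1 h, so it is taken at -1 + 24 = +23 h from the start of chemotherapy. With a multi-day regimen this could be during chemotherapy rather than after it ends.

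**3. What is the exception?** If chemotherapy is postponed together with the missed capsule, a next-day capsule is still taken beforehand and no conflict arises. The footnote does not limit itself to that case.

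**4. Does another section override the footnote?** Section 5.4, on adherence, contains no missed-dose rule. Section 5.2.2 covers discontinuation for adverse events only. Nothing forbids a late capsule.

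**5. How many patients could it touch?** The Protocol gives no missed-dose rate. Over an assumed range of 0 to 5%, with 93 patients per arm (Section 10.1), the number is 0 to 0.05 × 93 = 4.65 per arm. One patient is 1/93 = 1.08 percentage points of an arm's complete response rate. These figures count patients who could be touched. They do not estimate bias, since a late capsule need not change how the patient is classified.

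**The case against.** **The footnote may be inert.** Its wording presupposes repeated dosing and reads like carry-over from a daily-dosing template. Its opening sentence also sends the reader back to what the protocol requires, which is a capsule before chemotherapy. This makes a deliberate catch-up rule unlikely. It does not remove the instruction, which is current text on an active flowchart row.

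**The label sentence has another context.** Section 1.3.1 makes the statement while discussing double-dose NEPA in a second cycle. That is true, but what it calls off-label is use after chemotherapy, and a late first capsule is such use.

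**Stronger readings.** A reader might infer four further things, none of which the Protocol supports.

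- *That the footnote also schedules a late dexamethasone injection.* Dexamethasone is given intravenously (Section 5.1), whereas the footnote addresses what the participant takes. The concern is confined to the capsule.
- *That a late capsule would count as compliant and stay in the per-protocol set.* Section 9.7 classes any departure from protocol requirements as a deviation, and Section 10.3 admits to that set only those who adhered fully. Missing the pre-chemotherapy slot breaches Section 5.2.1 whatever happens the next day.
- *That the 7-day endpoint clock would restart at the late capsule.* At +23 h the window would then run to 23 + 168 = 191 h and omit 23 of the 24 acute hours. But dexamethasone is also a study drug; given on schedule, it starts the clock on the chemotherapy day. Section 2.2.4 describes its overall period as post-chemotherapy. No text tells an analyst to count from the later component.
- *That the D1 ticks, with the synopsis phrase, schedule a second capsule.* That would be 2 × 0.3 = 0.6 g netupitant and 2 × 0.5 = 1.0 mg palonosetron. Every operative dosing passage gives one capsule. Since D0 is headed baseline, the two ticks could simply mean dispensing on D0 and dosing on D1. The synopsis phrase is a separate, small inconsistency.

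**Conclusion.** The concern holds in a limited form. Footnote i is a stated rule that is wrong for this regimen: followed after a missed capsule, it leads to NEPA after chemotherapy has started, against the restriction reported in Section 1.3.1. This does not depend on whether D0 or D1 is the dosing day. It does assume that chemotherapy goes ahead as planned.

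The point is minor. Misses should be few for a dose given around an infusion, and the 0 to 5% range is an assumption. No material effect on the complete response rate, the per-protocol set or the non-inferiority conclusion is shown, and no direction of bias is claimed. The reason to act is patient safety.

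**What to change.** Replace footnote i with a rule for a single dose, for example:

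> Single dose before chemotherapy. If it is not taken before chemotherapy starts, do not give it later; manage per guideline and record a protocol deviation. The endpoint is counted from the start of chemotherapy.

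Label the dosing day in the flowchart, and tick dispensing and compliance on that day only. As a minor consistency edit, delete the words 'or double' from the synopsis research question.

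The cost is wording only: one footnote, one column label, two ticks and one synopsis phrase. No visits, patients or analyses are added.
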